### Intervention group

To determine the content of the RTG training, the therapist will initially assess the patient’s attempt of the whole task, and analyze which of its components need to be prioritized for practice. For example, a patient with weak shoulder flexion may practice reaching by sliding the hand forward over a non-resistant surface to touch an object or grasp it. The training tasks should be challenging and progressively adapted by chaining; that is by practicing first one part, then practicing that part along with the next [50]. Patients showing sufficient improvement may progress in this way to mastery of the whole task.

To optimally standardize the intervention, a detailed description of the underlying principles of the task-specific RTG intervention has been developed using the ‘essential components’ of the RTG movement as a structure [51] (see Additional file 1). An exercise manual containing 122 exercises has been produced for therapists to follow (see Additional file 2). Each exercise involves interacting with objects and the environment, and is set up to promote practice with joint range and speed of the movement, that is, close to those characteristics of the task when performed as a whole RTG action. The therapist can individualize exercises for patients by advising on or providing environmental adaptations; for example, by choosing meaningful objects of different sizes, weight, and shape, or by recommending a starting position for the patient. Little or no manual guidance will be used. Over the course of the feasibility study, further exercises may be incorporated as new ones are determined by working with the study participants.

Starting in the week after baseline assessment, participants allocated to the RTG training will receive 14 visits, each lasting 1 hour, from a research therapist over a period of 6 weeks. This will replace any usual care training for the upper limb. The frequency of the research therapist’s visits will be three times a week for the first 3 weeks, twice a week for each of the next 2 weeks, then once in the final week. The frequency of visits is tapered with the aim of increasing self-efficacy in practice. The intensity of practice within each 1-hour session will be dependent on individual participant’s capabilities, but high numbers of repetitions will be encouraged, with the aim of delivering between 100 and 300 repetitions within each 1-hour session, in accordance with the findings of a recent feasibility study into frequency of task-specific training [52]. To facilitate such a high number of repetitions, clinical experience has indicated that it is appropriate to limit the number of exercises prescribed within each session to a maximum of six, and to a maximum of four for participants to continue to practice independently. The research therapist will keep a log of which exercises from the treatment manual are performed, and of the number of repetitions of each exercise.

From the beginning of the intervention phase, the participants will be instructed to practice in the absence of the therapist for 1 hour/day. They will be asked to record on a log sheet the number of repetitions of each task that they complete in their independent practice. There is no method in place in this feasibility study to check on the fidelity of these records, as this would have required resources beyond those available for this study. The therapist will stress to the participant that an accurate record is important to enable us to determine the feasibility of the amount of practice prescribed. They will be requested to record reasons for non-adherence to the practice schedule. This information will be collected at the end of the intervention period.

To help participants understand the importance of practice for recovery and to promote compliance with the RTG task-specific training, a booklet about recovery from stroke will be provided (see Additional file 3). The booklet describes in simple terms the mechanisms of stroke and the potential for recovery by ‘rewiring’ in the brain through practice, and also provides contact details of local resources and services for people with stroke. A recent Cochrane review on information provision for patients with stroke and their caregivers showed that providing information improves patient and carer knowledge of stroke, improves aspects of patient satisfaction, and reduces patient depression scores [53].

Participants receiving the RTG training will be asked their opinions of the intervention using a structured questionnaire administered face to face by the research physiotherapist after their final intervention visit. With limited personnel to carry out these interviews, the risk of bias inherent in using the research therapist for these interviews was considered preferable to requiring the assessor to do these interviews, as this could cause unblinding. Data from the interviews will inform the acceptability of the intervention content and frequency.

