Hubbard has recommended that to have the best chance of being effective, task-specific practice should be intensive [15]. Decisions about the frequency of the intervention therefore need to reflect the amount of therapy that can be reasonably delivered by community therapy services and how much patients can be asked to practice in the absence of a therapist. The Extremity Constraint Induced Therapy Evaluation (EXCITE) trial of constraint induced movement therapy for the upper limb, which resulted in significant improvement in outcome, delivered 60 hours of supervised therapy over 2 weeks to participants at 3 to 9 months post-stroke [29]. To approach the same number of hours with a schedule that is more likely to fit within the constraints of UK community rehabilitation, it was decided that a prescription of 14 visits of 1 hour each over the course of 6 weeks with up to 1 hour a day of self-monitored practice should be used. Combined with the therapist-supervised sessions, the total prescription will be 56 hours of practice.

Before designing a definitive trial, the acceptability of the intervention, the characteristics of the participating population, recruitment and retention rates, descriptive estimates of outcome, and incidence of adverse events (AEs) need to be determined. This paper outlines the objectives and design of a feasibility study, and describes how the data generated will be used to inform a Phase 3 trial.

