### Study objectives

The aims of this feasibility trial are as follows.

1. To determine the characteristics of the sample entering the feasibility trial for its representation of the target population and to determine the most appropriate primary outcome measure for the sample, that is, the Action Research Arm Test (ARAT) or the Wolf Motor Function Test (WMFT).

2. To estimate identification and recruitment rates for the trial across multiple sites.

3. To determine the frequency and content of upper-limb treatment delivered to both the intervention and control groups.

4. To estimate the adherence of RTG group participants to the prescribed schedule.

5. To estimate the completeness of outcome data.

6. To calculate sample sizes for a subsequent definitive trial, based on measured changes in performance for both the control and intervention groups.

7. To collect and synthesize the views from participants in the intervention group to determine acceptability of the RTG therapy.

8. To determine the frequency of AEs in both groups.

9. To collect data on health and social care resource use to inform data-collection methods for an economic evaluation in the subsequent definitive trial.

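### Independent-practice adherence (42 of the 56 prescribed hours) rests on unchecked participant logs with no interim collection described, although the research therapist makes 14 home visits

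*Protocol article*

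**What the plan says.** Aim 4 under Study objectives is: "To estimate the adherence of RTG group participants to the prescribed schedule". The prescription has two parts. In the Intervention group section, participants "will receive 14 visits, each lasting 1 hour, from a research therapist over a period of 6 weeks", spread as "three times a week for the first 3 weeks, twice a week for each of the next 2 weeks, then once in the final week". From the start of treatment, "the participants will be instructed to practice in the absence of the therapist for 1 hour/day". The Background adds the two parts together: "the total prescription will be 56 hours of practice".

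The parts are recorded differently. The therapist logs the exercises and repetitions done at visits. For practice alone, participants "record on a log sheet the number of repetitions of each task that they complete in their independent practice", and they also write down why practice was missed. On accuracy, the section is open: "There is no method in place in this feasibility study to check on the fidelity of these records". It gives limited resources as the reason, and adds that the therapist will impress on participants the need for an accurate record. The paragraph ends: "This information will be collected at the end of the intervention period".

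The Data analysis section measures compliance by therapist visits (how many and how long) and by the share of participants who finish the six weeks. It also summarizes independent practice against what was intended, and reports withdrawals with their reasons.

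**The concern.** The log is the only described source for the independent-practice part of aim 4. The protocol itself says that an accurate record is needed to judge whether the prescribed amount of practice is feasible. The one collection time it gives is the end of the six weeks, and no step is described for securing the log of someone who stops before then.

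Two errors become possible. First, entries for several weeks can be written from memory shortly before hand-over. Second, a participant who stops in week 2 or 3 may never hand over a sheet or a reason. The second error would fall mainly on those who practised least, so an average over returned logs would be too high. Late-filled entries could also lean towards the prescribed amount, although the documents hold no evidence on that.

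At stake is the practice prescription for the definitive trial: an overstated figure could make an unachievable amount look feasible. Participants who give up practice are also the ones whose reasons are most useful for revising the intervention.

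**Working it through.** **Plan's own figures**
- Visits (Intervention group): 3 × 3 + 2 × 2 + 1 × 1 = 14. This reproduces the stated 14.
- Independent practice (Intervention group): 6 weeks × 7 days × 1 h = 42 h.
- Total: 14 + 42 = 56 h. This reproduces the figure in the Background.
- Share resting on the participant log: 42/56 = 75%. The other 14/56 = 25% rests on the therapist's own record.

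**Back-fill window**
- Hand-over only at the end would leave up to 6 × 7 = 42 days of entries open.
- Hand-over at each visit would leave an average of 42/14 = 3 days, and about a week in the final, once-weekly stretch.

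**Possible effect of missing logs (assumed inputs)**

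The RTG arm is about 50/2 = 25, from Participant recruitment and the 1:1 ratio in Randomization. The documents give no stopping rate and no practice level, so everything else here is assumed. Suppose *k* of *n* participants stop and leave no log, finishers achieve a fraction *a*, and stoppers a fraction *s*. An average over returned logs then gives *a*. The average over everyone is [(n − k)a + ks]/n, so the overstatement is (k/n)(a − s).

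Illustration: finishers do 30 of 42 h (71.4%) and stoppers do 10 h (23.8%).

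| Stoppers | Mean over all 25 | % of 42 h | Returned logs only | Gap (points) |
|---|---|---|---|---|
| 3 | (22 × 30 + 3 × 10)/25 = 27.6 h | 65.7% | 71.4% | 5.7 |
| 5 | (20 × 30 + 5 × 10)/25 = 26.0 h | 61.9% | 71.4% | 9.5 |
| 8 | (17 × 30 + 8 × 10)/25 = 23.6 h | 56.2% | 71.4% | 15.2 |

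Wider range: k = 2 to 6, a = 70% to 90%, s = 20% to 40%.
- Smallest gap: (2/25)(0.70 − 0.40) = 0.024, or 2.4 points (1.0 h of 42).
- Largest gap: (6/25)(0.90 − 0.20) = 0.168, or 16.8 points (7.1 h of 42).
- If no log is lost (k = 0), the gap is zero.

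**Possible effect of over-reporting (assumed inputs)**

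Take true independent practice at 50% to 70% of 42 h and logs inflated by 10% to 40%. All 14 visits are assumed attended.
- Low end: true total 14 + 21 = 35.0 h; reported 14 + 21 × 1.1 = 37.1 h; excess 2.1 h.
- High end: true total 14 + 29.4 = 43.4 h; reported 14 + 29.4 × 1.4 = 55.16 h; excess about 11.8 h.

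These sums are in hours, while the log is described as recording repetitions. They therefore assume that the sheet also yields time, or that the two move together.

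**The case against.** **The sentence may not cover the log sheets.** It directly follows the request to note why practice was missed, so it could mean those reasons alone, and it does not exclude earlier collection. This stands as a caution. A reader might infer that logs are definitely gathered at the end and at no other time, but the text does not say so. Even on the narrow reading, the reasons still wait until the end. The hand-over of the logs is then simply not described, and an article may leave that to operating procedures.

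**The lack of checking is declared.** It is an open, reasoned trade-off in a feasibility study and not an oversight. That stands for verification. It does not explain late collection, because a therapist is already in the home and taking a sheet needs no new contact.

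**Nothing says early stoppers are dropped.** This is correct. A reader might infer that they vanish from aim 4, or that the whole aim is unsound. Visit counts and durations, completion of the six weeks and study withdrawals with reasons do not depend on the logs, and they do cover such participants. They do not measure independent practice, however, and a person can give up practising without leaving the study.

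**The size is assumed.** This also stands. The gaps need every stopper's log to be lost and only returned logs to be averaged; the documents state neither.

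**Collection at visits is imperfect and late.** Entries could still be filled in just before a visit, and regular collection may itself prompt practice. Trial status reports 46 of 50 enrolled, so about 4/2 = 2 new RTG participants remain, plus any still in treatment. These points limit the gain in this trial but leave the gain for the definitive trial.

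**Conclusion.** The point holds for the independent-practice part of aim 4, which is 42 of 56 hours. That part depends on unverified self-records. The stated collection time is the end of the six weeks (for the reasons certainly, for the logs on the natural reading), and no use of the 14 visits for interim collection is described. This leaves room for back-filling over weeks, and it risks missing logs and practice-specific reasons from those who stop early.

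The likely direction is upward, because those who stop are both the least adherent and the least likely to return a log. The documents cannot fix the amount. The range of 2.4 to 16.8 points is conditional on assumed stopping and practice rates, complete loss of stoppers' logs and an average over returned logs only. It is not an estimate of bias in this trial. Nor do the documents show that any log has been lost or any entry invented. The supervised part of adherence, completion and withdrawals are sound on this point. It is a cheap improvement in data capture and not an error that invalidates the aim.

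**What to change.** Replace the last sentence of the paragraph on independent practice in the Intervention group section with a rule on these lines: at every scheduled visit the research therapist collects or photographs the current log sheet and any reasons for missed practice, and issues a fresh sheet; the same is done at the last contact with anyone who stops. Report independent-practice adherence for all RTG participants, together with the number whose logs are missing or incomplete. How days after stopping are counted can be left to the analysis plan.

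**Cost.** A minute or so at visits that already take place, with no extra visits or staff. Regular collection may slightly encourage practice, so it should be described as part of the procedure and carried unchanged into the definitive trial. Because 46 of 50 participants are already enrolled, the change reaches only those remaining and the later trial. Record the date of the change so that logs gathered under the two arrangements can be told apart.

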### Control group

The control group will receive arm therapy in accordance with usual care, which will be delivered by NHS service therapists. In usual care, the frequency and content of physiotherapy or occupational therapy for improving upper-limb function is variable. From consultation with local therapy services, we found that provision of therapy varies in intensity, depending on the individual’s care pathway and the range of community services available. For example, after discharge from early supported discharge services, patients with care needs are usually referred to community intermediate care or rehabilitation teams. These teams typically provide a service for 6 weeks, and patients may receive approximately two visits per week from a qualified therapist, with 30 minutes of the visit focused on the arm or hand. There may be supplementary visits from support workers. Other patients may be seen by a community therapist once a fortnight with no supplementary visits from support staff, and some patients may not receive any therapy at all. It is unusual to receive arm therapy beyond 6 months after discharge from hospital. One of the aims of this feasibility study is to determine the frequency and content of treatment delivered in both arms of the trial. Usual care will be captured on recording sheets that will be completed by NHS service physiotherapists and occupational therapists. They will be asked to record the content, duration, and frequency of upper-limb treatment, including the number of repetitions of any functional task training on treatment recording sheets developed by Donaldson *et al*. [54].

Participants allocated to the control group will be provided with a booklet about recovery after stroke, which is the same as the booklet which will be given to the intervention group, with the exception that, instead of information about the RTG training, it will provide details of the frequency of assessment visits for the study (see Additional file 4).

Participants in the control group who do not receive any therapy aimed at improving upper-limb function during their participation will receive a single visit from the research physiotherapist after their final assessment. The physiotherapist will discuss the patient’s functional limitations and goals with them and, after assessing their movement and function, will provide specific exercises and advice. If indicated, the physiotherapist is able to refer to appropriate local therapy services.

### Adverse events

Pain in the shoulder, upper arm and hand and oedema in the hand are common sequelae of hemiparesis, and are therefore expected AEs in the study. In addition, falls and equipment failure leading to injury requiring a visit to hospital or general practitioner will be treated as expected AEs. It is possible that increased use of the upper limb may lead to an increase in general activity in the home or community, and could result in increased likelihood of falling. The ARAT and WMFT assessments require that equipment is taken into the participant’s home. Although every effort will be made to minimize risk, accidents may happen when using any equipment. Participants will be specifically asked at each of the assessment visits if they have experienced any of the expected AEs.

All staff involved in contact with participants will receive training on identification and reporting of AEs. Any serious AEs that occur will be reported to the trial sponsor, and if the chief investigator (CI) considers any of these to be related to the RTG intervention, these AEs will be reported immediately to the research ethics committee that granted approval for the trial. Incidence of AEs will be collected by the trial manager and reported quarterly to the trial steering group.

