### Participant recruitment

Participants will be recruited from the stroke services of three National Health Service (NHS) Hospital Trusts and community therapy services, covering an area with a population of 918,300 [30]. This trial intends to recruit 50 participants over a period of 15 months. Eligibility criteria are designed to be as inclusive as possible to promote the applicability of the evidence to service delivery.

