### Randomization

Participants will be randomly allocated to the intervention or to the usual care groups in a 1:1 ratio after baseline assessment. Randomization will occur via an independent internet-based service, and the procedure will use minimization to balance time since stroke, severity of upper-limb impairment, and group numbers between the two arms. Time since stroke will be categorized as less than or equal to 3 calendar months post-stroke, or more than 3 calendar months post-stroke. This 3-month cut off was chosen to balance between groups the number of participants within 3 months of stroke, who might be recovering at a faster rate [46]. Baseline severity will be categorized using scores on the ARAT in three subgroups defined by Morris *et al*. [47] (group 1: score 0 to 3; group 2 score 4 to 28; group 3 score 29 to 56).

The data for the randomization procedure will be entered by the trial manager. He will have no influence over the allocation to group because the randomization procedure is independent, and he will not be involved in measuring outcome. Post-randomization, the trial manager will contact the patient and any NHS services involved in the patient’s care to inform them of the treatment allocation.

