### Data analysis

As this is a feasibility study to test the levels of recruitment and retention of participants, and completeness of data that can be expected within a definitive multicenter trial, there will be no formal statistical testing, and results will instead be summarized using descriptive statistics.

Analysis of the centrally held screening log data will lead to a description of the characteristics of the recruited sample against the target population, and the percentage of refusals at the recruitment stage. Recruitment rates per month for each site will be determined. The number of withdrawals and reasons for withdrawal from the study will be assessed.

Compliance with the RTG intervention will be assessed by the number and duration of physiotherapy visits and the proportion of participants completing the 6-week intervention. The frequency of use of the exercises, number of repetitions, and duration of practice of each exercise, both within the physiotherapy sessions, and the independent practice will be summarized and compared with the intended exercise frequency and content. The frequency and content of the treatment received by each group will be summarized, as will the incidence of expected AEs and serious AEs. Responses to the participant questionnaire about the RTG training will be synthesized and examined to determine if any changes should be made to the intervention.

Completeness of outcome data will be determined, and data for each of the endpoints will be summarized; the mean differences between the arms, with their confidence intervals, will be presented. Assessment of the sample scores on the outcome measures, combined with a summary of participant preference for ARAT and WMFT, will be carried out to determine which arm function test should be used as the primary outcome measure for a phase III trial. Sample sizes for a subsequent phase III trial will be calculated, based on observed changes from baseline in performance, for both the control and intervention groups.

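### The falls item in the expected-AE list is ambiguous and, on its natural reading, too narrow for the risk of more frequent falling that the protocol links to the training

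*Protocol article*

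**What the plan says.** The Adverse events section of the protocol article lists arm and hand pain and hand oedema as expected AEs, with no severity threshold, and attributes them to hemiparesis. It then adds that "falls and equipment failure leading to injury requiring a visit to hospital or general practitioner will be treated as expected AEs". Equipment accidents are tied to the ARAT and WMFT kit taken into the home. Falling is the only listed harm linked to the effect of training: more use of the arm may lead to more general activity, which "could result in increased likelihood of falling".

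Two further statements rest on that list. In the same section, "Participants will be specifically asked at each of the assessment visits if they have experienced any of the expected AEs". In Data analysis, the quantities to be summarized include treatment received, "as will the incidence of expected AEs and serious AEs". Aim 8 under Study objectives is "To determine the frequency of AEs in both groups".

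There is a second, general route: "All staff involved in contact with participants will receive training on identification and reporting of AEs", and AE incidence goes through the trial manager to the steering group each quarter. The article does not define a fall or say how a fall without injury is recorded.

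**The concern.** The harm named is a higher likelihood of falling. The matching measure is the number of falls, or of people who fall. On the natural reading, the item records the much narrower set of falls followed by an injury and a hospital or GP visit. Because the prompted question and the named summary use the same list, a fall outside that set is neither asked about nor summarized unless it is serious.

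The information at stake is fall frequency in each arm, which a definitive trial would need in order to plan its safety monitoring. A low count of medically attended falls says little about how often people fell. Trial monitoring and management also dispenses with an independent safety committee, partly because intervention-related AEs are thought very unlikely, so the descriptive AE summary carries more weight.

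The wording is also open to two readings, so the meaning of the final count depends on which one was applied.

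**Working it through.** **Step 1: the two readings.**

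- *Reading A:* the injury-and-visit clause qualifies both falls and equipment failure. A fall without a hospital or GP visit is then not an expected AE. It is not prompted and, unless serious, not in the named summary.
- *Reading B:* the clause qualifies equipment failure alone. Every fall is then an expected AE, prompted at each assessment and summarized. The gap disappears.

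Reading A is the more natural, since the two nouns are joined ahead of one shared qualifier. Nothing in the article rules out B.

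**Step 2: the fallback under reading A.** The remaining route is unprompted reporting by staff in contact with participants. The Intervention group section gives RTG participants 14 home visits in 6 weeks. The Control group section says that usual care varies and that some patients may have no therapy. Opportunities to notice a minor fall therefore differ by arm, whereas the assessment visits are the same for both.

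**Step 3: size, as an illustration.** The plan gives no fall rate, so there is no figure to reproduce. Inputs from the document:

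- Sample size: "This trial intends to recruit 50 participants over a period of 15 months".
- Allocation: "in a 1:1 ratio after baseline assessment", so 50 / 2 = 25 per arm.
- Follow-up: 6 months (Outcome measurement). With no loss to follow-up, 25 × 0.5 = 12.5 person-years per arm.

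*Falls.* Assumed, not in the documents: 1 to 3 falls per person-year, and 5% to 25% leading to a hospital or GP visit.

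- All falls per arm = 12.5 × rate: 12.5 × 1 = 12.5 to 12.5 × 3 = 37.5.
- Medically attended falls per arm = 12.5 × rate × fraction: 12.5 × 1 × 0.05 = 0.6 to 12.5 × 3 × 0.25 = 9.4.
- At 2 per person-year and 10%: 25 falls, of which 2.5 are counted.
- Approximate 95% interval for the rate ratio under equal rates = exp(±1.96 × √(2/count)). With 25 per arm it is 0.57 to 1.74; with 2.5 per arm it is 0.17 to 5.8. This is a large-sample Poisson formula, unreliable at 2.5 events, and clustering within repeat fallers would widen both intervals.

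*Fallers.* Assumed: 6-month control risk of 20%, 40% or 60%; risk ratio 1.5; 10%, 25% or 50% of fallers meeting the threshold. Expected fallers = 25 × p, and P(none in an arm) = (1 − p)^25.

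| Control risk | All fallers (control / RTG) | 50% counted | 25% counted | 10% counted | P(none in RTG) at 10% |
|---|---|---|---|---|---|
| 20% | 5 / 7.5 | 2.5 / 3.75 | 1.25 / 1.9 | 0.5 / 0.75 | 47% |
| 40% | 10 / 15 | 5 / 7.5 | 2.5 / 3.75 | 1 / 1.5 | 21% |
| 60% | 15 / 22.5 | 7.5 / 11.25 | 3.75 / 5.6 | 1.5 / 2.25 | 9.5% |

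**Step 4: what full counting would buy.** With all fallers counted, the 95% half-width for the risk difference, 1.96 × √(p₀(1−p₀)/25 + p₁(1−p₁)/25), is 24, 27 and 22.5 percentage points for the three rows, against assumed differences of 10, 20 and 30 points. Full counting describes frequency better, but the comparison stays imprecise.

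**The case against.** The strongest objection is reading B, under which all falls are already prompted and summarized. That stands, and it is why the point concerns ambiguity and the natural reading rather than a proven exclusion. It also argues for settling the wording.

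Second, this is a journal article. The full protocol, the AE form or a standard operating procedure may define a fall, and a trained assessor carries out the visits at which the question is asked, so it need not vary by site. This also stands. But the article does state a capture rule, and it is the wording of that rule that is at issue, not missing detail.

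Third, general AE reporting exists and is not limited to expected events. True, but it is unprompted, lies outside the named summary, and is likely to be fuller in the RTG arm.

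Fourth, medically attended falls are better remembered and easier to verify. Minor falls would rest on recall over up to three months by unmasked participants, some with aphasia or cognitive impairment. This is a real limitation, and a reason to keep medically attended falls as a separate count.

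A reader might go further and infer that the study can hardly see the risk it names, or that counted falls will be a handful at most. The documents do not support that. They give no fall rate, the assumed ranges reach 9.4 counted falls per arm, injurious falls are counted in both arms, and no formal testing is planned. Nor do they show that a low count would be presented as evidence of no fall risk.

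**Conclusion.** The point holds as a wording defect with a cheap remedy. The falls item can be read two ways. On the more natural reading, prompted and summarized falls are limited to medically attended injuries, which is too narrow for the stated risk of more falling and for aim 8. The remaining route for other falls is likely to favour detection in the RTG arm; this is inferred from its visit schedule, not shown by data.

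The size cannot be fixed from the documents. On the assumed ranges, expected fallers per arm drop from 5 to 22.5 with all fallers counted to roughly 0.5 to 11 under the threshold. With 25 per arm, no definition gives a precise between-arm comparison, so the gain is a usable description of fall frequency. On reading B there is no loss of data, only a sentence to clarify.

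**What to change.** - Reword the list so that all falls are an expected AE and the injury-and-visit clause applies to equipment failure only.
- At each assessment visit after randomization, ask every participant how many falls they have had since the last visit, and how many led to an injury needing a hospital or GP visit.
- Report the number of falls and the number of fallers by arm, with medically attended falls as a separate category.
- Trial status reports 46 participants already enrolled. Record the date of the change, make clear which visits used which question, and carry the definition into the definitive trial.

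The cost is two numeric fields at visits already planned and a little more recording. The downside is that minor falls are recalled less well than injurious ones and are self-reported by participants who know their allocation, so the all-falls count should be presented with that caveat.
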